**Tools**
*Adverse Childhood Experience Questionnaire:* This is a 10-item questionnaire designed for administration to people aged ≥18 years. Questions cover family dysfunction; physical, sexual, and emotional abuse and neglect by parents or caregivers; peer violence; witnessing community violence; and exposure to collective violence [36]. It is a reliable [37] and valid [38] tool for the measurement of childhood trauma and negative health outcomes in adulthood. This was effectively used in exploring whether individuals exposed to physical and sexual abuse in childhood or domestic violence–prone environments are more likely to be involved in intimate partner violence (IPV) later in their life [39].*Conflict Tactics Scale-2 (CTS-2):* The CTS-2 (an updated version of the CTS tool) is a self-report 39-item survey measuring both the extent to which partners in a dating, cohabiting, or marital relationship engage in psychological and physical attacks on each other and their use of reasoning or negotiation to deal with conflicts [40]. Scoring for the CTS-2 involves assigning numerical values to responses and calculating subscale sores. Each question on the CTS-2 asks the participant to report the frequency of a specific behavior in the past year, with responses including 0=this has never happened, 1=once in the past year, 2=twice in the past year, 3=three to 5 times in the past year, 4=six to 10 times in the past year, 5=eleven to 20 times in the past year, 6=>20 times in the past year, and 7=not in the past year but it did happen before. To calculate a subscale score, the scores for each item in that subscale are added together. The CTS-2 has been shown to be valid and demonstrates reliable stability across its subscales: psychological aggression (*r*=0.69), physical assault (*r*=0.76), injury (*r*=0.70), and negotiation (*r*=0.60). However, the reliability coefficient for sexual coercion is noticeably weaker (*r*=0.30) [41].*Posttraumatic stress disorder (PTSD) checklist for Diagnostic and Statistical Manual of Mental Disorders (DSM)-5 (PCL-5):* The PCL-5 is a 20-item self-report measure that assesses the presence and severity of PTSD symptoms [42]. Items on the PCL-5 correspond with DSM-5 criteria for PTSD. The PCL-5 can be used to quantify and monitor symptoms over time, to screen individuals for PTSD, and to assist in making a provisional or temporary diagnosis of PTSD. The PCL-5 is composed of 20 items, each from 0 (not at all) to 4 (extremely). The total score for PCL-5 is calculated by adding together the scores for each of the 20 items. Each item is scored between 0 and 4, so the total score will range from 0 to 80. A cut-off score of 33 is often used, suggesting a high likelihood of PTSD [43]. The PCL-5 exhibits robust reliability, with impressive internal consistency (Cronbach α=0.94) and notable test-retest reliability (*r*=0.82) [42] and validity [44]. Furthermore, there was a strong relationship between current PTSD symptoms and meeting criteria for all 4 DSM-5 PTSD symptom clusters in women with IPV-caused brain injury [45].*Generalized Anxiety Disorder Scale (GAD-7):* The GAD-7 is a 7-item self-report inventory used for measuring the severity of anxiety [46]. The questions ask about common symptoms of anxiety the participant had during the past 2 weeks, such as worrying, being restless, being easily annoyed, and fearing. Each question is rated on a scale of 0 to 3, with higher scores indicating higher levels of anxiety. The total score ranges from 0 to 21. The GAD-7 is a quick and reliable tool for identifying the presence and severity of generalized anxiety disorder symptoms [46].*Patient Health Questionnaire-9 (PHQ-9):* The PHQ-9 is a 9-item self-report measure used to assess the levels of depression. The questions ask about common symptoms of depression the participant had during the past 2 weeks, such as feeling hopeless, having little energy, and difficulty concentrating [47]. Response options range from 0 (not at all) to 3 (nearly every day). The total score for the PHQ-9 ranges from 0 to 27, with higher scores indicating greater severity of depressive symptoms [48]. The validity and reliability of the PHQ-9 have been established in various studies [48]. The PHQ-9 questionnaire has been used to evaluate depression symptoms in individuals who have experienced IPV [49].*Alcohol Use Disorders Identification Test (AUDIT):* The AUDIT is a 10-item screening tool developed by the World Health Organization [50] to assess alcohol consumption, drinking behaviors, and alcohol-related problems. Each item in this tool is evaluated on a 0 to 4 scale, and the total score can range from 0 to 40 [51]. It is a valid and reliable tool for measuring alcohol-related problems [52].*Somatic Symptom Severity Scale (PHQ-15):* The PHQ-15 is a 15-item questionnaire that assesses somatic symptoms of pain across different body systems [53,54]. The tool uses a rating scale ranging from 0 (not at all) to 2 (nearly every day), and total scores range from 0 to 30, with higher scores indicating more severe somatic symptoms [54,55]. The PHQ-15 is a reliable tool with a test-retest reliability of *r*=0.60 [56]. It has also been used to show that survivors of IPV have greater levels of somatic symptoms [57].*International Trauma Questionnaire (ITQ):* The ITQ is an 18-item questionnaire that assesses PTSD and complex PTSD [58]. The reliability of the ITQ has been well established, as evidenced by several publications [59,60]. Furthermore, it has been used in studies to assess the relationship between complex PTSD and the severity of IPV psychological perpetration [61,62].*Brief Irritability Test (BITe):* The BITe is a 5-item questionnaire assessing common feelings of irritability [63]. The BITe consists of questions regarding how the individual has felt in the past couple of weeks, and they rate their experience on a scale from 1 (not at all) to 6 (always). The score ranges from 5 to 30, with higher scores indicating higher levels of irritability.*Level 2-Substance Use-Adult:* This questionnaire is a 10-item screening tool developed by the US National Institute on Drug Abuse to assess substance use [64]. The participant rates each item on a 5-point scale, from 0=never to 4=nearly every day. Scores on the individual items are interpreted independently because each item inquires about the use of a distinct substance. The rating of multiple items at scores >0 indicates greater severity and complexity of substance use.

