### Statistical Analysis

The objective of this project is to evaluate the efficacy of a CSN intervention for women who have experienced IPV-BI. This will be accomplished by quantitatively measuring resiliency, QoL, and neurocognition before and immediately after the intervention. A follow-up assessment will occur 3 months after the completion of the intervention to evaluate the maintenance of any gains in function. The mean (or median) for each assessment will be compared across testing times using 1-way ANOVAs. Relationships between BISA scores and the change scores for each assessment will be evaluated using regression analysis. Furthermore, the outcome of the intervention will be compared among various subgroups based on the findings of various mental health screening tools (eg, participants with PTSD vs participants without PTSD), substance use, and adverse childhood experience (eg, participants with adverse childhood experience vs participants without such experience). Various demographics and mental health screening assessments will be used to control for nonspecific effects of IPV. In addition, we will have opportunities to better characterize IPV-BI based on the BI load from the BISA tool, findings of various mental health screening tools, and cognitive findings using the Creyos assessment and task-switching paradigm. The α value will be set a priori at *P*<.05. All data will be analyzed using SPSS (IBM Corp).

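### The example subgroup comparisons split graded screening scores into yes/no groups, which costs efficiency for those associations; regression on the score, as already planned for BISA, would avoid it

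*Protocol article*

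**What the plan says.** The Statistical Analysis section of the protocol article plans to compare the outcome of the intervention among subgroups formed from the mental health screening tools, substance use and adverse childhood experience. Two splits are given as examples: "participants with PTSD vs participants without PTSD" and "participants with adverse childhood experience vs participants without such experience".

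The instruments are described under Mental Health Screening Tools (Textbox 3). Of the PCL-5 it says "so the total score will range from 0 to 80", and also "A cut-off score of 33 is often used, suggesting a high likelihood of PTSD". Of the Adverse Childhood Experience Questionnaire it says "This is a 10-item questionnaire designed for administration to people aged ≥18 years"; no scoring rule is given.

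Two other sentences in the Statistical Analysis section bear on the point. For brain injury load the plan is regression: "Relationships between BISA scores and the change scores for each assessment will be evaluated using regression analysis". The screening measures also have a second role: "Various demographics and mental health screening assessments will be used to control for nonspecific effects of IPV". Whether they enter that adjustment as continuous or categorical variables is not stated.

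**The concern.** The section treats two similar questions differently. BISA, a score from 0 to 8, is related to change by regression. PTSD symptoms, measured on a scale from 0 to 80, appear in the subgroup example only as present or absent. Cutting a graded score in two treats all women on one side of the cut as alike. If change varies smoothly with the score, that throws away part of the association being sought.

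At stake is the chance of seeing, among about 100 women, whether those with more symptoms or more childhood adversity change more or less than others. The loss grows as the split becomes lopsided. That is possible in a sample recruited for partner violence and brain injury, but the article gives no prevalence for either factor.

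**Working it through.** **The plan's own figure.** Sample Size Estimation states N = 100, more than 90% power and a two-sided 5% level for a change score. No effect size or SD is given, so the figure can be inverted but not reproduced: d = (1.960 + 1.282)/√100 = 0.324 (0.327 with the t distribution). It concerns change across testing times and says nothing about subgroup comparisons.

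**Inputs.** From the article: N = 100, two-sided 5%, PCL-5 range 0 to 80, cut-off 33, 10 childhood items. Assumed, because the article does not give them: the score distribution, the share of women above a cut, a linear relation, the correlation between score and change, and 100 complete cases.

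**Efficiency of a split.** For a normal score with a proportion p on one side of the cut, the squared correlation between the score and its yes/no version is

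E = φ(z_p)² / [p(1 − p)].

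Under a linear relation, E is the fraction of efficiency kept. At p = 0.5: 0.3989²/0.25 = 0.637. At p = 0.9: 0.1755²/0.09 = 0.342.

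**Power.** The correlation r becomes r√E after the split. By Fisher's z, power = Φ(atanh(r)·√(N − 3) − 1.960). With r = 0.3 and the continuous score: 0.3095 × 9.849 − 1.960 = 1.088, so power is 86%. At a 50/50 split, r√E = 0.3 × √0.637 = 0.239, and power is 67%.

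| Split | Efficiency kept | Loss | Effective n of 100 | Power, r = 0.3 | Power, r = 0.2 |
|---|---|---|---|---|---|
| none (continuous) | 100% | 0% | 100 | 86% | 52% |
| 50/50 | 64% | 36% | 64 | 67% | 35% |
| 70/30 | 58% | 42% | 58 | 63% | 33% |
| 80/20 | 49% | 51% | 49 | 56% | 28% |
| 90/10 | 34% | 66% | 34 | 42% | 21% |

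**Check on the PCL-5.** Normal scores were simulated, rounded, truncated to 0–80 and cut at 33. With assumed means of 25 to 50 and SDs of 15 to 20, the share at or above 33 ran from 31% to 88% and the loss from 33% to 61%. This agrees with the table.

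**Check on childhood adversity.** Any versus none is not a cut on a normal score, so a 0–10 item count (itself an assumption) was given a beta-binomial distribution with assumed means of 2 to 5. The share with any experience ran from 53% to 98% and the loss from 51% to 90%. For this split the loss can exceed the top of the table.

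**The case against.** The strongest reply is that the loss figures are not in the documents. No distribution, prevalence or correlation is given, and if the true effect is a step at a clinical threshold, the split loses nothing of this kind. That stands, and the figures are conditional on the stated assumptions.

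It can also be said that the splits are only examples, that the Abstract foresees regression among various variables, and that an analysis plan not shown may add continuous analyses. This lowers the weight of the point. It does not remove it: both stated examples are binary, and regression is specified only for BISA. A comparison of women with and without PTSD is also easy for clinicians to read, which is a fair reason to keep showing it.

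A reader might infer more than the article supports:

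- *That the trial discards a third to two thirds of what it collects.* It does not. Full scores are recorded, the screening measures also serve as control variables, and the main pre-post comparison is untouched.
- *That every screening tool could be used as a continuous score.* The Level 2-Substance Use items are each interpreted on their own, without a total.
- *That separate tests within each subgroup are planned.* The text describes a comparison among subgroups.
- *That the PTSD definition is an error because two instruments could supply it.* Besides the PCL-5, the article says "The ITQ is an 18-item questionnaire that assesses PTSD and complex PTSD". Which instrument and cut-off define the subgroup is detail that an article may leave to the analysis plan.
- *That the analysis would show who benefits.* In a single-arm study neither the split nor the regression can do that.

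**Conclusion.** The point holds as a minor one about the choice of analysis. The article's example subgroup comparisons dichotomise graded measures although regression on a score is already planned beside them. Under normality, linearity and splits from 50/50 to 90/10, about 36% to 66% of the efficiency for these associations is lost. With r = 0.3 and 100 complete cases, power falls from 86% to between 67% and 42%. For any versus no childhood adversity the loss may be larger. The comparisons are supplementary, the stated power does not refer to them, and no main result depends on the change.

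**What to change.** For measures with a total score, such as the PCL-5 total or the childhood experience item count, regress the change score on the continuous score, or regress the follow-up value on the score with adjustment for the baseline value. Take one moderator at a time and label the analyses exploratory, as an extension of the BISA regression. Show the PTSD and childhood-experience groups descriptively alongside. Keep categorical handling for the substance-use items, which have no total. State that the results are associations with change, not differential benefit, because there is no control group.

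The change is one of wording and needs no new data. It costs a check of linearity and a summary that is slightly harder for clinicians to read, which the descriptive groups partly offset.

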### Objectives

The *primary objectives* of this study protocol are as follows:

To measure the efficacy of the CSN rehabilitative intervention in terms of its impact on resiliency, QoL, and neurocognitive functionsTo evaluate the feasibility of the CSN rehabilitative intervention in terms of study recruitment, adherence, and retention

The *secondary objectives* of this study protocol are as follows:

To characterize neurocognitive function in women who have experienced IPV-BITo characterize mental health consequences in women who have experienced IPV-BI

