
#### Outcome Measures

The following outcome measures, which will be administered by a trained member of the research team, will be used to assess resiliency, QoL, and neurocognitive function:

*Resiliency:* Resiliency will be characterized using the Connor-Davidson Resilience Scale [65]. This 25-item questionnaire measures responses to 5 factors associated with resilience on a 5-point Likert scale ranging from 0 (not true at all) to 4 (true nearly all the time). The scale has been shown to have good psychometric properties, with high internal consistency and test-retest reliability [65].*QoL:* QoL will be measured using a modified version of the Medical Outcomes Study short form-36 [66]. This 36-item questionnaire consists of 8-scaled scores covering several aspects of QoL and general health. Each scale is scored separately and transformed onto a scale that ranges from 0 to 100 for ease of comparison, with lower scores indicating a lower QoL.*Neurocognition:* Neurocognitive function will be assessed using the Creyos (formerly known as Cambridge Brain Sciences) tool [67], which consists of 12 different tasks that assess aspects of cognition, including reasoning, memory, attention, and verbal ability. The tasks include digit span, double trouble, feature match, grammatical reasoning, monkey ladder, odd one out, paired associates, polygons, rotations, spatial planning, spatial span, and token search. The tasks have been validated in studies of patients, in brain imaging studies of healthy volunteers, and in several large-scale public studies [67-69]. The Creyos tool maintains a global normative database of >75,000 participants that allows for detailed comparisons of individuals to specific populations. The tests have been shown to be valid and reliable, and a meaningful change can be calculated using the normative database [67]. Notably, all tasks, which users report to be fun and engaging, will be administered through web application or in person using a desktop or laptop and require no expert technical support to administer. Task results will be stored securely in the cloud and can be easily downloaded for offline analyses [65,69].

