In addition to the tasks included in the Creyos tool, a task-switching paradigm will be used to probe executive functions [70]. A simplified version of the task that is run on an Android tablet will be used to capture executive dysfunction in this study. This simplified version has been implemented in a study (unpublished) examining head impacts and concussions in ice hockey players.

Furthermore, we will have access to the following measures collected throughout the intervention, which are incorporated within the BEARS program [23]:

*Traumatic BI-QoL (TBI-QoL) measurement system:* The TBI-QoL measurement system is a recently developed QoL measure specifically designed for people who have experienced TBI. It consists of a 20-item questionnaire covering the domains of physical health, emotional health, cognitive health, and social participation [71]. The findings of this tool would be helpful in corroborating the findings of the study short form-36.*Brainex cognitive assessment:* This is a series of tests of neurocognitive function, including assessments of symbolic thinking. The findings of this tool will be helpful in strengthening the findings of the Creyos assessment.*Functional performance indicators:* The functional performance indicators are independently derived by ABI Wellness and act as additional composite scores that are purely indicative and aim to reflect the ability of the individual to function in everyday life. The scores are created from various TBI-QoL subdomains, which were chosen to best reflect these functional performance measures.*ABI Wellness overall engagement:* The overall engagement assessment is done to provide an overview of the weekly and cumulative engagement across the different activities of the ABI Wellness 4-pillar program. The engagement is measured against the personal goal of each activity set by the facilitator.

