### Sample Size Estimation

To generate and design a study with adequate power, we estimated the required sample size based on previous data from our laboratory in both healthy participants and those with IPV-BI [34,35]. Power calculations are based on the desired end point to detect a change in each of the assessments across testing times. Therefore, assuming our published SDs for these measures and considering the potential for increased variability in this study population, a total sample size of 100 participants would provide a >90% probability that the study will detect a significant change score at a 2-sided 5% significance level.

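### The primary efficacy objective is tested on at least 22 scores, each at P<.05, with no primary score per domain, no error control and no rule for calling a domain improved

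*Protocol article*

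**What the plan says.** Objectives, first primary objective: "To measure the efficacy of the CSN rehabilitative intervention in terms of its impact on resiliency", followed by quality of life and neurocognitive function. The three domains are not ranked.

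Outcome Measures sets out the scores:
- **Resiliency:** one 25-item scale, counted here as one total.
- **Quality of life:** "This 36-item questionnaire consists of 8-scaled scores covering several aspects of QoL and general health". The scales are scored separately and no summary score is named.
- **Neurocognition:** the Creyos tool, "which consists of 12 different tasks that assess aspects of cognition", with no composite named. In addition, "a task-switching paradigm will be used to probe executive functions".

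Statistical Analysis compares each assessment across the testing times by 1-way ANOVA and fixes one threshold: "The α value will be set a priori at" P<.05. Regressions on BISA scores and comparisons among subgroups are described in the same paragraph.

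Sample Size Estimation rests on the same scheme: "Power calculations are based on the desired end point to detect a change in each of the assessments across testing times". It claims that "a total sample size of 100 participants would provide a >90% probability" to "detect a significant change score at a 2-sided 5% significance level".

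Feasibility Measures refers to primary outcome measures in the plural when it defines retention. The article does not say which scores these are.

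**The concern.** The article anticipates concluding that the program improves resiliency, quality of life and neurocognition. For resiliency the evidence is one test. For quality of life it is eight tests, and for neurocognition at least thirteen, each at an unadjusted 5%. Without a named score or a decision rule, a reader of the results cannot tell whether one significant scale out of eight, or one task out of thirteen, was meant to count as an improved domain. Some significant scores are to be expected by chance even if nothing changes. An efficacy signal carried forward to the planned comparative study could rest on one of them.

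**Working it through.** **The plan's own figure.** Sample Size Estimation gives N = 100, power above 90%, two-sided 5%. It states no effect size or SD, so the figure cannot be reproduced. Inverting the paired normal formula gives the standardised change it implies:

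dz = (1.960 + 1.282)/√100 = 0.324 SD of change.

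That calculation is for a single score at an unadjusted 5%.

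**Count of scores (from Outcome Measures).** 1 + 8 + 12 + 1 = 22. This leaves out the resilience factors, the measures collected within the BEARS program, the regressions and the subgroups.

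**Independent scores, valid test for each, no true change.**
- Either direction: 1 − 0.95^22 = 0.676
- False improvement only: 1 − 0.975^22 = 0.427
- 8 quality-of-life scales, either direction: 1 − 0.95^8 = 0.337
- 13 neurocognitive scores, either direction: 1 − 0.95^13 = 0.487
- Three scores, one per domain, unadjusted: 1 − 0.95^3 = 0.143

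**Correlated scores.** The document gives no correlation between scores, so a range of equal correlations ρ is assumed. With c = 1.96 and k scores,

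P(at least one) = 1 − ∫ φ(u) [Φ((c − √ρ·u)/√(1−ρ)) − Φ((−c − √ρ·u)/√(1−ρ))]^k du.

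For false improvement the second Φ term is dropped.

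| Set of scores | ρ = 0 | ρ = 0.3 | ρ = 0.5 |
|---|---|---|---|
| All 22, either direction | 0.68 | 0.57 | 0.44 |
| All 22, false improvement | 0.43 | 0.30 | 0.22 |
| 8 quality-of-life scales, either direction | 0.34 | 0.30 | 0.25 |
| 13 neurocognitive scores, either direction | 0.49 | 0.42 | 0.33 |

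The first row falls below one half at ρ of about 0.41.

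**Effect of the ANOVA as worded.** The same women are measured three times. A simulation (100 women, 3 times, 22 independent scores, 2,000 runs per setting) compared an unpaired 1-way ANOVA with a repeated-measures ANOVA.

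| Within-woman correlation | Familywise error, unpaired | Familywise error, repeated measures |
|---|---|---|
| 0 | 0.68 | 0.68 |
| 0.3 | 0.30 | 0.70 |
| 0.5 | 0.055 | 0.68 |
| 0.7 | 0.002 | 0.66 |

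An unpaired analysis would hide the inflation by being conservative. Pairing the analysis brings it out.

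**Price of error control.** Detectable change at 90% power, noncentral t, two-sided:

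| Women analysed | At 0.05 | At 0.05/3 (first Holm step) |
|---|---|---|
| 100 | 0.327 | 0.373 |
| 80 (assumed) | 0.367 | 0.419 |

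A Bonferroni correction over all 22 scores (0.05/22 = 0.00227) would cost much more. By the normal formula, power at dz = 0.324 falls to 57.5%, and 90% power needs dz = 0.433.

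**The case against.** **An analysis plan that is not shown may deal with this.** Multiplicity adjustment is often left to that document, and the plural reference to primary outcome measures suggests that a designation may exist. This would settle the matter if the article were merely silent. It is not: it fixes one threshold for all tests and bases the sample size on an unadjusted 5% for each assessment. A later plan with error control would need a different power statement.

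**The study is early and uncontrolled.** It is meant to support later comparative trials, so strict control over every score is partly a matter of preference. That stands, and it is why the remedy controls three scores and not 22.

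**The anticipated claim is joint.** If all three domains must show a result, the error when nothing changes is small. With independent scores it is 0.05 × 0.337 × 0.487 = 0.008, and at ρ = 0.5 it is 2.7%. A reader might infer that any one of the 22 scores suffices for the efficacy claim, but no passage says so. The defect is that the rule is unstated. The inflation remains for separate claims about quality of life and neurocognition.

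**The regressions and subgroups are not clearly efficacy tests.** The abstract describes the regressions as exploratory. They are left out of the count of 22. Counting three pairwise time contrasts per score as 66 independent tests would also go too far. The plan specifies an ANOVA across times, and within a score the third contrast is the difference of the other two.

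**Conclusion.** The point holds in this form: at least 22 scores serve the primary efficacy objective, each at P<.05, with no primary score per domain, no error control and no stated rule for calling a domain improved. With a valid paired analysis, no true change and equal between-score correlation from 0.5 to 0, the chance of at least one P<.05 is about 0.44 to 0.68 in either direction, against 0.05. For false improvement it is about 0.22 to 0.43, against 0.025. Within domains, in either direction, it is about 0.25 to 0.34 for quality of life and 0.33 to 0.49 for neurocognition.

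A reader might infer that a false efficacy finding is more likely than not. The documents do not support that. The 0.68 needs independent scores and counts deterioration as well as improvement. Scores from the same women are likely to be positively correlated, and false improvement stays below one half at every correlation examined. Nor do these figures describe an unpaired 1-way ANOVA, which would be conservative. They apply once the analysis respects the pairing.

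**What to change.** For the post-minus-pre contrast, prespecify one score per domain:
- the resilience scale total;
- one SF-36 summary or scale;
- one Creyos composite, such as the mean of the 12 standardised task scores.

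Test the three with a paired analysis and Holm at an overall two-sided 5%. Claim improvement only for domains that pass. Report all other scales and tasks, the follow-up contrasts, the BISA regressions and the subgroups as secondary or exploratory, with estimates and 95% confidence intervals. Restate the power in Sample Size Estimation for the three named scores at the adjusted level, and use the same names for the primary outcome measures in Feasibility Measures.

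The change is to wording and needs no new data. Only 6 women had been enrolled by October 2023, so at that stage it could be made before most outcomes accrue. The cost is sensitivity: the detectable change at 90% power rises from about 0.33 to at most 0.37 SD of change with 100 analysed, or from 0.37 to at most 0.42 if 80 are analysed (an assumption). Results on a single scale or task could no longer carry an efficacy claim by themselves unless that score was the one named.
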